## Interventions

### Explanation for the choice of comparators {6b}

There are two active and one sham stimulation interventions delivered to three parallel groups. Active transspinal stimulation is delivered while standing with BWS and/or in the supine position. Sham transspinal stimulation is delivered while standing with BWS. All participants undergo the same locomotor training intervention. The guarantee of locomotor training and the 2:1 ratio of active to sham stimulation reduce the risk of people refusing to participate in the trial. For the sham protocol, the stimulator frequency and waveform is identical to active stimulation, but the intensity is held at the motor threshold for only 1 min, followed by a gradual return to no stimulation for the subsequent 29 min. Studies have suggested that this pattern of stimulation can mimic the initial sensation of stimulation followed by the acclimation to cutaneous stimulation. This approach is expected to improve blinding to active versus sham stimulation.

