### Outcomes {12}

#### Primary outcomes

The primary outcomes are neurophysiological biomarkers that accurately probe corticospinal and spinal neuroplasticity (at presynaptic and postsynaptic motoneuron levels):Corticospinal neuronal excitability:

We establish the active MEP threshold that corresponds to the intensity that evokes 10 responses of at least 50 mV following 20 1-ms transcranial magnetic stimulation (TMS) pulses in seated subjects. Then, the soleus MEP recruitment input–output curve is assembled while maintaining small-amplitude contractions. During BWS-assisted stepping, MEPs are recorded at 1.3 times the right soleus MEP active threshold randomly at different phases of the step cycle (divided into 16 equal bins or time windows) based on the signal from the right foot switch. During stepping, MEPs are collected before and after intervention using Lokomat settings matched to the baseline, while an effort is made to record MEPs using Lokomat settings matched to those of the last training session. This establishes changes at matched settings and adaptations during more demanding stepping conditions. MEPs recorded at different stimulation intensities (recruitment curve) are measured as peak-to-peak amplitude and normalized to the soleus maximal M-wave (Mmax) evoked by posterior tibial nerve stimulation to counteract differences in muscle fiber composition across subjects. Stimulation intensities are normalized to the intensity corresponding to the 50% of the MEPmax amplitude, estimated based on the sigmoid function fit to the data. For the participants who have obtainable soleus MEPs at baseline, the main outcomes from this experiment are the MEPmax from the MEP recruitment curves and the MEP amplitude at the mid-stance and mid-swing phases before and after the intervention.2)Spinal neuronal excitability:*2a) Soleus H-reflex rate-dependent (or homosynaptic) depression*: To assess restoration of homosynaptic depression exerted at the synapses between muscle spindle primary Ia afferents and alpha motoneurons, soleus H-reflexes following posterior tibial nerve stimulation at the popliteal fossa with a 1-ms pulse are recorded from seated subjects at different frequencies (1.0, 0.33, 0.2, 0.125, and 0.1 Hz). Homosynaptic depression is greatest at 1.0 Hz and fully recovers at 0.125 and 0.1 Hz [69]. Homosynaptic depression cannot be recorded during stepping because it is abolished by strong spinal inhibitory circuits and efferent activity. The main outcome measure from this neurophysiological biomarker is the soleus H-reflex 1.0/0.1 Hz ratio [70].*2b) Soleus H-reflex depression by antagonistic nerve stimulation*: To examine the restoration of reciprocal inhibitory actions on antagonistic alpha motoneurons, the soleus H-reflex is conditioned by common peroneal nerve (CPN) stimulation at conditioning-test (C-T) intervals of 0, 1, 2, 3 and 4 ms, with subjects seated [71–75]. Reproducible CPN conditioning stimulation is ensured by using a stable, small-amplitude TA M-wave and similar soleus M-wave amplitudes under control and conditioning stimulations. Soleus H-reflexes are measured as peak-to-peak amplitude, accepted for M-waves ranging from 2 to 8% of the maximal M-wave (Mmax), and normalized to the Mmax. The main outcome is the amplitude of the conditioned soleus H-reflex as a percentage of the control H-reflex. The C-T interval for which reciprocal inhibition is present or reciprocal facilitation is the smallest is further investigated during BWS-assisted stepping. The main outcomes are the conditioned H-reflex at rest and during the stance and swing phases of BWS-assisted stepping, which both reflect the amount of reciprocal inhibition.*2c) Control and conditioned soleus H-reflexes during stepping*: During standing with BWS as needed, the soleus H-reflex and M-wave recruitment curves are assembled. Then, each participant steps with the assistance of the Lokomat, and soleus H-reflexes are recorded under control conditions and following CPN conditioning stimulation randomly across 16 equal time bins into which each step cycle is divided based on the signal from the foot switch [75]. The tibial nerve stimulation intensity is adjusted in real-time online to evoke H-reflexes such that their corresponding M-waves are 2–8% of the Mmax evoked 80 ms after the test H-reflex at each bin (Fig. 3). Control and conditioned soleus H-reflexes during stepping are collected before (baseline) and 1–2 days after completion of all 40 intervention sessions at Lokomat settings matched to baseline and the last training session. This approach determines changes at matched settings and reflex adaptation at more demanding settings [76]. During stepping, soleus H-reflexes are measured as peak-to-peak amplitude, accepted for M-waves ranging from 2 to 8% of the Mmax, normalized to the Mmax, and averaged for each bin of the step cycle. The main outcome is the control and conditioned soleus H-reflex amplitude normalized to the Mmax at mid-stance and mid-swing phases.

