### Sample size {14}

Our study is powered to establish and detect a significant effect size across the 3 groups between pre- and post-intervention. We performed statistical analysis of the preliminary data utilizing G*Power-3 software [88, 89]. The sample size was calculated to obtain a power larger than 0.8.

*Aim 1:* Determine if priming locomotor training with transspinal stimulation increases MEP amplitudes and promotes appropriate MEP amplitude modulation during stepping. The TA MEPmax amplitudes recorded in 10 healthy subjects while at rest were compared before and after 10 sessions of transspinal stimulation delivered with subjects lying supine (difference between means: 148.05, pooled standard deviation: 206.8, d = 0.71). To predict sample size at a power of 0.80 at α = 0.05 using repeated measures, within-between interaction ANOVA across 3 groups, 24 total subjects are needed. We will enroll 45 subjects, so we will be adequately powered even if subjects drop out at a higher than expected 20% rate. This sample size is based on results from healthy control subjects and not from SCI subjects.

*Aim 2*: Determine if priming locomotor training with transspinal stimulation restores spinal inhibition, reduces neurophysiological hyperreflexia, and re-establishes H-reflex modulation during stepping. The soleus H-reflex rate-dependent depression in 6 persons with SCI was recorded at 1.0 Hz from the left leg and compared before and after 15 sessions of transspinal stimulation. Based on the soleus H-reflex recorded at 1.0 Hz before and after transspinal stimulation (difference in means of pre versus post: 25.28, pooled standard deviation: 28.92), the effect size was 0.87. To predict sample size at a power of 0.80 at α = 0.05 using a one-way ANOVA across 3 groups, 18 total subjects are needed. We will enroll 45 subjects, so we will be adequately powered even if subjects drop out at a higher than expected 20% rate.

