The soleus H-reflex amplitude during assisted stepping in 11 persons with motor incomplete SCI (AIS C-D) recorded from the right leg was compared before and after locomotor training [26]. Based on the amplitude of the soleus H-reflex at mid-stance before and after training (difference in means of pre versus post: 13.67, pooled standard deviation: 17.4), the effect size was 0.79. To predict sample size at a power of 0.80 at α = 0.05 using a one-way ANOVA across 3 groups, 21 total subjects are needed. We will enroll 45 subjects, so we will be adequately powered even if subjects drop out at a higher than expected 20% rate.

Limb coordination relies on the strength of reciprocal inhibition between antagonistic muscles. We used data from a study performed by our group that examined short-latency inhibition from ankle flexor afferents onto ankle extensor motoneurons at rest in 13 persons with AIS C-D SCI before and after locomotor training [28]. Based on the amplitude of the conditioned H-reflex at the conditioning-test interval of 2 ms before and after training (difference in mean of pre versus post: 15.04, pooled standard deviation: 17.21), the effect size was 0.874. To predict sample size at a power of 0.80 at α = 0.05 using a one-way ANOVA across 3 groups, 18 total subjects are needed. We will enroll 45 subjects, so we will be adequately powered even if subjects drop out at a higher than expected 20% rate. Please note that the established power was based on data from SCI subjects who received either transspinal stimulation or locomotor training separately and not combined.

*Aim 3*: Determine if priming locomotor training with high-frequency transspinal stimulation improves limb coordination and the ability to stand and walk. These are secondary measures, and the study is not powered based on these outcomes.

Collectively, an average of 6 to 8 subjects per group is needed to establish significant differences for primary outcomes before and after transspinal stimulation or locomotor training. By enrolling 15 participants per group, the study will be robustly over-powered to detect these differences despite a projected possible 20% dropout rate, sporadic missing data values, or lower-than-expected observed effect sizes.

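### The sample-size section claims power for three-group comparisons, but all four planning effects are single-group pre-post changes, two of them after the training every arm receives, and they appear to have been converted to the wrong effect-size scale

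*Protocol article*

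**What the plan says.** Sample size {14} sets the target as an effect across the three groups from before to after the intervention, with power above 0.8. It uses four planning effects.

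- **Aim 1, MEPmax.** "The TA MEPmax amplitudes recorded in 10 healthy subjects while at rest were compared before and after 10 sessions of transspinal stimulation"; the figures are "difference between means: 148.05, pooled standard deviation: 206.8, d = 0.71". The conclusion is that, "using repeated measures, within-between interaction ANOVA across 3 groups, 24 total subjects are needed".
- **Aim 2, H-reflex rate-dependent depression.** Six persons with SCI before and after 15 sessions of transspinal stimulation ("difference in means of pre versus post: 25.28, pooled standard deviation: 28.92"; effect size 0.87). One-way ANOVA across three groups, total 18.
- **Aim 2, mid-stance H-reflex.** Eleven persons with SCI; the amplitude "recorded from the right leg was compared before and after locomotor training" (13.67/17.4; effect size 0.79). One-way ANOVA, total 21.
- **Aim 2, reciprocal inhibition.** Thirteen persons with SCI before and after locomotor training (15.04/17.21; effect size 0.874). One-way ANOVA, total 18.

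The section concludes that "an average of 6 to 8 subjects per group is needed to establish significant differences for primary outcomes", and that 15 per group is more than enough even with 20% dropout.

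Explanation for the choice of comparators {6b} states: "All participants undergo the same locomotor training intervention". Under Primary outcomes, the MEP endpoint has a restricted analysis set: "For the participants who have obtainable soleus MEPs at baseline, the main outcomes from this experiment are the MEPmax".

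**The concern.** The hypotheses in Objectives {7} are comparative: active against sham, and standing against supine. Trial design {8} assesses superiority, and Statistical methods {20a} tests group, time and their interaction. The quantity to plan on is therefore the difference between arms in change. No such difference appears in the sample-size section.

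A pre-post change after locomotor training is expected in all three arms. It cancels from the between-arm contrast, so its size says nothing about what stimulation adds. The totals also look too small for the effects quoted, which suggests that a standardised mean difference was put on the wrong scale.

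What is at stake is how the result is read. If standing versus sham, or standing versus supine, shows no difference, a trial described as over-powered will be taken as evidence of no effect, when its power for that contrast may be about one half or lower.

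**Working it through.** **Inputs.** From Sample size {14}: d = 148.05/206.8 = 0.716 (stated as 0.71); 25.28/28.92 = 0.874 (stated as 0.87); 13.67/17.4 = 0.786 (stated as 0.79); 15.04/17.21 = 0.874. Alpha 0.05, power 0.80, three equal groups, 45 enrolled, and 45 × 0.8 = 36 after 20% dropout. The protocol gives no pre-post correlation ρ, so ρ is an assumption throughout. Totals are rounded up to multiples of three.

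**Step 1: reproduce Aim 2.** One-way ANOVA, noncentrality λ = f²N, degrees of freedom 2 and N − 3. Entering d itself as f gives the protocol's totals:

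- f = 0.87: N = 18 (power 0.855)
- f = 0.79: N = 21 (power 0.854)
- f = 0.874: N = 18 (power 0.858)

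Cohen's f is the standard deviation of the group means divided by the within-group SD, so it is not d. For two equal groups f = d/2. For three groups with one differing from the other two by d, f = d√2/3.

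| Stated d | Protocol N | N with f = d/2 | Power at 45 | N with f = d√2/3 | Power at 45 |
|---|---|---|---|---|---|
| 0.87 | 18 | 57 | 0.71 | 63 | 0.66 |
| 0.79 | 21 | 66 | 0.62 | 75 | 0.57 |
| 0.874 | 18 | 54 | 0.72 | 60 | 0.66 |

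The reproduction needs no correlation. The corrected totals take the pooled SD as the SD of the analysed variable; for change scores this means ρ = 0.5, because SD of change = SD × √(2(1 − ρ)). For the two training-based rows they also credit stimulation with the whole training effect.

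**Step 2: reproduce Aim 1.** Within-between interaction with two time points: λ = f² × N × 2/(1 − ρ), degrees of freedom 2 and N − 3. With f = d/2 = 0.355 to 0.358 and ρ = 0.5, N = 24 (power 0.83–0.84), and N = 21 falls short (0.77). For example, λ = 0.358² × 24 × 4 = 12.3. This f is the time effect when every group changes by d.

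**Step 3: Aim 1 with an interaction f.** The interaction f is the SD of the three arm-specific changes divided by 2. If both active arms change by d and sham by 0, f = (d√2/3)/2 = d/√18 = 0.167 to 0.169. The same f applies if one arm differs from the other two in the opposite direction.

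| ρ (assumed) | N needed | Power at 45 | Power at 36 |
|---|---|---|---|
| 0.3 | 123–126 | 0.36 | 0.29 |
| 0.5 | 90 | 0.48 | 0.39 |
| 0.7 | 54–57 | 0.71 | 0.59–0.60 |
| 0.8 | 39 | 0.88 | 0.78–0.79 |

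A graded pattern (d, d/2, 0), closer to the standing-over-supine hypothesis, needs 117–120 at ρ = 0.5.

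**Step 4: the within-arm reading.** For a paired t-test, the standardised change is d/√(2(1 − ρ)), which equals d at ρ = 0.5. The numbers needed are 18 per arm at d = 0.71, 15 at 0.79 and 13 at 0.87, not 6 to 8. A higher correlation would lower them, but none is stated.

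**Step 5: the Aim 1 denominator.** The MEP outcome covers only participants with an obtainable baseline soleus MEP, while the calculation counts all 45. The protocol gives no expected proportion. If it were 60% to 80% (assumption), 27 to 36 would be evaluable. Power at ρ = 0.5 for the Step 3 pattern would then be 0.29 to 0.39 before dropout.

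**The case against.** Several points on the other side have weight.

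**24 does not prove the wrong f.** A reader might infer that 24 can arise only from a time-effect f. It cannot be put that strongly: the correct interaction f of about 0.167–0.169 also gives 24 at a correlation of about 0.88–0.89. The d/2 reading with ρ = 0.5 is the more plausible, but it is an inference.

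**90 is conditional.** A reader might conclude that the trial needs 90 participants. That holds at ρ = 0.5 with the stated pattern. At ρ = 0.8, 39 suffice and 45 gives power 0.88. The documents do not settle which correlation applies.

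**Two effects do come from stimulation.** The MEPmax and rate-dependent-depression effects follow transspinal stimulation without locomotor training. If stimulation adds to training, they could stand in for active versus sham. It would therefore be too strong to say that the calculations bear only on within-arm change. It would also be too strong to say that training gains in the sham arm must shrink the contrast, since that requires less-than-additive effects and the protocol anticipates synergy. Even so, these two effects give no standing-versus-supine difference.

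**Some limits are disclosed.** The section admits that Aim 1 uses healthy subjects and that Aim 2 uses treatments given separately, and it words the 6-to-8 figure as a before-and-after difference. It does not say that the data contain no between-arm contrast, and it still claims adequate power for three groups.

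**Rest versus contraction is unsettled.** Primary outcomes describes soleus MEPs during small contractions, while Participant timeline {13} mentions recording at rest. Little should rest on that mismatch. The differences in muscle (TA against soleus) and population stand.

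**Conclusion.** The concern holds for the claims of adequate power and over-powering. No planning effect is a between-arm difference in change, and the two training-only effects cannot inform one. That part needs no assumption.

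The Aim 2 conversion is the firmest numerical error: 18, 21 and 18 match d entered as f. On the d/2 scale the totals are 54 to 66, and with one arm differing by the full d they are 60 to 75, with power at 45 of 0.57 to 0.66. Those corrected figures take the pooled SD as the SD of the analysed variable.

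For Aim 1, power at 45 runs from 0.36 to 0.88 as the correlation goes from 0.3 to 0.8, if both active arms change by the full d and sham by nothing. The supportable conclusion is that power for the between-arm contrast has not been demonstrated and may be about one half. It is not that 45 is inadequate in every case. The 6-to-8 figure is unsupported as a between-arm number, and as a within-arm number at correlation 0.5.

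**What to change.** Leave enrolment unchanged and rewrite Sample size {14}:

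1. Withdraw the totals 24, 18, 21 and 18, the 6-to-8-per-group figure, and the statements that the trial is adequately or more than adequately powered.
2. Give the detectable between-arm difference in change (or the power) at 45 and at 36, over a stated range of pre-post correlation. Name the assumed pattern of arm changes and use the f that belongs to the test.
3. Present Aim 1 separately on the expected number of participants with obtainable baseline soleus MEPs, and state that expectation.
4. Say that pre-post effects of locomotor training are common to all arms and are not the planned between-arm effect. If the stimulation-only effects are kept as a proxy for active versus sham, state the additivity assumption.

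The analysis set and definition of the MEP outcome need not change. The cost is wording, and a stated power that is less favourable.

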### Recruitment {15}

In this mechanistic clinical trial, individuals with motor incomplete SCI will participate. In New York and New Jersey, 22,000 people live with SCI, while 600 new cases are reported every year. Given the SCI population within the NY Metropolitan area, recruitment of 45 persons with SCI will not be difficult. We will use diverse and multiple approaches to recruit participants, similar to those we have utilized for our ongoing clinical trials**.** We recruit persons with SCI from (1) the database and outpatients of the James J. Peters Veterans Affairs Medical Center in Bronx, NY, the second performance site, (2) via flyers at the NYC Spinal Cord Injury Association, (3) open houses of SCI Projects at Rutgers, (4) via flyers posted on the lab’s Facebook page, and from (5) outpatient Neurology and Rehabilitation departments of the Mount Sinai Medical Center in New York, NY. In addition, the PIs of the grant reserve booths at the Annual Abilities Expo, New Jersey Convention, and Expo Center every year. We will also use emails from our databases and advertisements in local newspapers to recruit participants.

## Assignment of interventions: allocation

### Sequence generation {16a}

To minimize imbalance between study groups, we performed block randomization with a block size of 9 to assign eligible participants into the 3 groups. If groups are not balanced, we ensure that the following blocked randomized subjects are stratified based on their ability to ambulate with assistive devices or not. We will also check after the completion of intervention by all subjects in each group, whether the groups are balanced or not regarding baseline motor function and perform tests of association accordingly. Blocked randomization is a commonly used randomization technique in clinical trials with a small sample size. This approach reduces bias and fosters balanced allocation of participants into different groups [90].

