### Trial design {8}

This is a mechanistic, sham-controlled, randomized, parallel design, multi-site (2 sites), clinical trial in which participants with chronic SCI are assigned in equal ratios to one of three study groups (or arms). Group 1: Active transspinal stimulation while standing followed by locomotor training; Group 2: Active transspinal stimulation while lying supine followed by locomotor training; and Group 3: Sham transspinal stimulation while standing followed by locomotor training. Study outcomes are assessed for superiority before (baseline) and after 40 sessions of primed locomotor training.

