## Methods: participants, interventions, and outcomes

### Study setting {9}

Neurophysiological assessments before and after 40 sessions of therapy are performed at the KLab4Recovery Research Program located at the College of Staten Island, City University of New York, New York, USA, an academic institution. Therapy and clinical assessments are performed at the KLab4Recovery Research Program and at one clinical research center (Spinal Cord Damage Research Center) of a government hospital (James J. Peters Veterans Affairs Medical Center, Bronx, New York USA). Both study sites are listed at ClinicalTrials.gov (https://clinicaltrials.gov/ct2/show/NCT04807764).

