For participants receiving transspinal stimulation while lying supine, hips, and knees are placed in slight flexion and stabilized by holsters and towels to avoid external limb rotations as needed (Fig. 2). For participants receiving active or sham transspinal stimulation while standing, BWS is provided in a standing frame or in the Lokomat to ensure safety (Fig. 2/1a). The initial BWS is adjusted such that knee buckling during standing is absent and decreases over the training course to achieve full body loading. Because prolonged standing may be demanding for individuals with SCI, a 2-min break is given every 10 min of standing.

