## Statistical methods

### Statistical methods for primary and secondary outcomes {20a}

For each dependent variable (primary and/or secondary outcome), descriptive statistics including frequencies and percentages for categorical variables and means and percentile distributions for continuous variables to examine the distribution of outcomes and describe the study population are performed.

We will group each dependent variable based on the time of testing (before and after the intervention) and the subject group (2 experimental, 1 sham). A two-way mixed analysis of variance (ANOVA) along with Bonferroni post hoc* t-*tests [93] at 2 3 levels (2: time, 3: groups) to test the main and interaction effects among subject groups and time will be performed separately for each outcome. Furthermore, repeated measures analysis of covariance (ANCOVA) will be performed for each outcome separately with gender, age, level of SCI, and clinically evaluated baseline walking function as separate covariates. Outcomes will not be analyzed based on SCI severity because the ISNCSCI scale does not correlate with improvements in walking ability [3], while age is considered one of the predictors of ambulation in SCI [94].

Mixed regression methods and analysis of slope and threshold of correlation will be used to establish the relationship between the ability to stand and walk, quality of life, and changes in primary outcomes (neurophysiological biomarkers). We will use an identity or log link based on the data distribution.

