## Oversight and monitoring

### Composition of the coordinating center and trial steering committee {5d}

The principal investigators (PIs) of this clinical trial are PI # 1, [name], PT, MBA, PhD, at the College of Staten Island, City University of New York, and PI # 2, [name], PhD, at Icahn School of Medicine at Mount Sinai and James J. Peters Veterans Affairs Medical Research Center (JJPVAMC). PI # 1 performs along with her research team at the Klab4Recovery all neurophysiological recordings before and after training for all study participants of the clinical trial to ensure consistent experimental procedures for all neurophysiological recordings. PI # 1 also leads the implementation of transspinal stimulation and locomotor training interventions, as well as the clinical assessments before and after training for study participants at Klab4Recovery. PI # 2 leads the implementation of transspinal stimulation and locomotor training interventions as well as the clinical assessments before and after training for study participants at JJPVAMC. Both PIs ensure that locomotor training and transspinal stimulation are implemented equivalently at both sites. The trial steering committee is composed of the PIs and dedicated research staff.

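### Two sites treat and score participants under different leads, but neither the stated randomisation nor the stated models include site; a site-by-time term would cheaply remove the effect of a chance arm-by-site imbalance.

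*Protocol article*

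**What the plan says.** All references are to the Protocol article.

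- **Where the work is done.** Study setting {9}: "Therapy and clinical assessments are performed at the KLab4Recovery Research Program and at one clinical research center", the latter in a government hospital for veterans. All neurophysiological assessments are made at the academic site.
- **Who leads it.** Composition of the coordinating center {5d}: one principal investigator leads the interventions, "as well as the clinical assessments before and after training for study participants at Klab4Recovery"; the other leads them, "as well as the clinical assessments before and after training for study participants at JJPVAMC". The same section says both leads ensure equivalent implementation across sites.
- **Randomisation.** Sequence generation {16a}: "we performed block randomization with a block size of 9 to assign eligible participants into the 3 groups". The only stratifier named is ambulation with or without assistive devices, and it is used only if the groups turn out unbalanced. The planned balance check concerns baseline motor function.
- **Analysis.** Statistical methods {20a}: a time-by-group mixed ANOVA for each outcome, and a repeated measures ANCOVA "with gender, age, level of SCI, and clinically evaluated baseline walking function as separate covariates". Section {20b} plans no additional analyses.
- **Assessment.** Plans for assessment {18a}: the same investigator, equipment and settings are used at baseline and after therapy.

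**The concern.** In a two-site trial of a hands-on intervention, the site can affect how much participants improve. The treating teams differ, and the participants and the scoring of improvement may differ too. With 15 participants per arm, chance can give the arms noticeably different site mixes. If mean change then differs between sites, part of that difference appears in the arm contrast. Even when the arms happen to be balanced, site variance stays in the error term.

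This is more than detail left to another document. The article names its stratifier, its balance check, its model and its four covariates, and site is in none of them. The outcomes most exposed are the clinical ones (walking, balance, questionnaires), which are assessed separately at each site. The primary neurophysiological outcomes are exposed only through treatment delivery and case mix.

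**Working it through.** **What can reach the treatment comparison.** The test of interest is time by group, which compares mean changes. If a site scores everyone higher by a constant *c* at both visits, the change is (post + *c*) − (pre + *c*) = post − pre, and *c* cancels. What remains is a site difference δ in mean change. If *a* and *b* are the numbers of second-site participants in two arms of 15, the shift in their contrast is δ × (*a* − *b*)/15.

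**Inputs**
- From the documents: 45 participants, three arms of 15, blocks of 9, two sites.
- Assumed, because not stated: one list not separated by site; sites entering in random order; 15 of 45 treated at the second site; δ = 0.5 SD of change.

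**Distribution of the gap.** With complete blocks each arm has exactly 15. When site order is random relative to the list, the second-site counts per arm follow

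P(x₁, x₂, x₃) = C(15, x₁) C(15, x₂) C(15, x₃) / C(45, 15), with x₁ + x₂ + x₃ = 15.

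- Var(x₁) = 15 × (1/3) × (2/3) × (45 − 15)/(45 − 1) = 2.27
- Cov(x₁, x₂) = −2.27/2 = −1.14
- Var(x₁ − x₂) = 2 × 2.27 + 2 × 1.14 = 6.82, so the SD is 2.61
- Mean absolute gap ≈ 0.8 × 2.61 ≈ 2.1 participants

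Simulated allocations agree:

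| 15 of 45 at second site | Gap of 4 or more | Gap of 5 or more |
|---|---|---|
| One named pair of arms | 18% | 8% |
| Worst of the three pairs | 36% | 21% |

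For the worst pair, the range over the assumed share is 28% and 12% with 10 participants at the second site, and about 42% and 23% with 22. With 36 participants left after the article's 20% dropout, the chance that the worst pair differs by one third of an arm or more is 17% to 32% for second-site shares of 20% to 50%. With 45 participants and blocks of 9 drawn within site, a gap of 30 percentage points or more essentially disappears (0% in simulation).

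**Shift in the contrast at δ = 0.5 SD**
- Average gap: 0.5 × 2/15 = 0.07 SD
- Gap of 4: 0.5 × 4/15 = 0.13 SD
- Gap of 5: 0.5 × 5/15 = 0.17 SD

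For a gap of 5, δ of 0.25 or 0.8 SD gives 0.25/3 = 0.08 or 0.8/3 = 0.27 SD.

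**Scale.** The standard error of a 15-against-15 contrast is √(2/15) = 0.37 SD, so 0.17 SD is a little under half a standard error. The planning effects in Sample size {14} are 0.71 to 0.874.

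**Precision.** At a one-third share and δ = 0.5 SD, unadjusted site adds 0.5² × (1/3) × (2/3) = 0.056 to a within-site variance of 1, or about 6%. Adjustment takes the error degrees of freedom from 45 − 3 = 42 to 41.

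**The case against.** The case on the other side is substantial, and much of it stands.

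- **List structure.** A reader might infer that all 45 were randomised in one stream across sites. The allocation sections do not say so; they leave open whether a list was kept per site. The probabilities above are therefore conditional. Even with separate lists, the stated models would still lack site.
- **Delivery.** The latitude in delivery, such as "BWS is provided in a standing frame or in the Lokomat to ensure safety" or anodes on the abdomen or the iliac crests, might be read as site differences. The text ties neither to a site: anode position follows participant comfort, and body weight support and guidance force follow an algorithm. The article also describes written intervention protocols, staff training, session logs and supervision by at least two authors. These measures may shrink a site effect, but they neither estimate it nor adjust for it.
- **Case mix.** The veterans' hospital is one recruitment source among several, and the article does not say where its outpatients are treated. Baseline walking function, age and injury level are already covariates and would absorb part of a prognostic difference.
- **Rating.** It is tempting to say that different raters at the two sites will appear as an arm effect. A constant offset cancels when the same investigator scores both visits. Only a difference in how change is scored remains, and only for the secondary clinical outcomes.
- **Bias.** Randomisation leaves the estimator unbiased over allocations, and the test's error rate already reflects chance imbalance. That is right. The cost is the conditional shift in the one allocation obtained, plus some precision.

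**Conclusion.** The point holds as a cheap improvement, not as an error that undermines the trial. Two sites under separate leads treat participants and score clinical outcomes, and site is in neither the stated stratification nor the stated models. For a single arm contrast the likely effect is small: about 0.07 SD on average, and 0.13 to 0.17 SD in the roughly one allocation in five or six where the gap reaches 4 or 5 participants. The 36% and 21% figures apply to the worst of three pairs and should not be read as the risk for a named comparison. All these figures rest on an unstratified list, random site order, a one-third share at the second site and a 0.5 SD site difference in change, none of which the article gives. The documents do not support a claim of systematic bias or of a demonstrated site effect.

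**What to change.** In Statistical methods {20a}, for every primary and clinical outcome, either add treatment site together with its site-by-time term to the mixed ANOVA, or fit an ANCOVA of the post-treatment value on baseline and group with site as a covariate. A site main effect alone is not enough: it adjusts the average level across visits and leaves the time-by-group test unadjusted. Report a table of arm by site. State in Sequence generation {16a} whether the list is kept by site.

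The cost is one degree of freedom per model and a sentence or two in the plan. It can be done before group codes are released, even if every block has been issued.

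Drawing blocks not yet issued within site is optional and applies only if the list is not already separated by site. Recruitment is due to end in about April 2025, so this may affect few participants, and incomplete last blocks could leave arm sizes off by one or two.
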